### Objectives

The aim of the present study is to evaluate the effectiveness of a structured group virtual SMS program as an add-on to treatment-as-usual (TAU) in a sample of adults with anxiety disorders. Primary questions: When group SMS is added to TAU in community-based care for patients with anxiety disorders, is the SMS + TAU group more effective in reducing anxiety symptoms than TAU alone? Secondary questions: a) Considering a recovery-oriented approach for patients with anxiety disorders, is there a significant difference between group SMS + TAU and usual care in terms of self-management strategies and personal recovery assessment at the 12-month follow-up? b) Does group SMS + TAU present superior cost-effectiveness and cost-utility, in terms of quality of life and anxiety-free days, than TAU for patients with anxiety disorders at the 12-months follow-up? c) Is there a significant difference between group SMS + TAU and usual care for high-end functioning rates? d) Is there maintenance of gains at 12- and 24-months follow-up? e) Is there differential effectiveness based on moderators (i.e., sociodemographic characteristics, clinical characteristics, past treatment experience) and mediators (i.e., group cohesion, therapeutic alliance, adherence)?

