##### Economic evaluation outcomes

The cost-effectiveness and cost-utility analysis will be carried out from health system and patient perspectives based on Canadian guidelines [77]. The 2-year costs considered will include all medical services and resources used during hospitalization, emergency department visits, outpatient visits, physician fees and outpatient medications. Patient out-of-pocket costs will include drug co-payments, payments to professionals not covered by the provincial public health insurance coverage, costs related to transportation and time spent by patients while seeking outpatient medical attention, as well as costs related to presenteeism and absenteeism [78]. Program costs associated with the training of facilitators and group meetings will include salaries, benefits, institutional overhead, and opportunity costs [79]. Generalized linear models (GLM) with log link and appropriate distribution (i.e., gamma) will be used to study the difference in costs (Beta estimates) as a function of the intervention (TAU vs SMS) while controlling for potential confounding study factors. Health outcomes will include symptom reduction (BAI) and health-related multi-attribute utility quality of life (AQoL-6D). The number of Anxiety-Free Days (AFD) will be calculated for each BAI scores with a value between 1 (‘anxiety free’) and 0 (‘fully symptomatic’) with linear interpolation to estimate the number of AFDs between baseline and follow up [80]. We will measure quality of life with the AQoL-6D to assess utility estimates [81]. For data analyses, repeated measures will be used to assess the difference (Beta estimates) in health outcomes as a function of the intervention and variables of interest. The incremental cost-effectiveness ratios (ICER) and incremental cost-utility ratios (ICUR) will be calculated based on beta estimates obtained. A discounting rate of 3.5% will be used for future values. We will carry out a sensitivity analysis for estimated values while considering a range of plausible values (95% CI). The ICUR will quantify the trade-off between costs and health-related quality of life.

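### The only uncertainty method stated for the ICER and ICUR, a 95% CI range around the estimates, is poorly matched to a superiority question and gives no usable range when the effect interval includes zero

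*Protocol article*

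**What the plan says.** The Objectives section of the protocol article asks whether SMS + TAU will "present superior cost-effectiveness and cost-utility, in terms of quality of life and anxiety-free days, than TAU for patients with anxiety disorders at the 12-months follow-up". This is a comparative question about value for money, put in terms of superiority.

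The section on economic evaluation outcomes sets out the analysis:

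- Costs: "Generalized linear models (GLM) with log link and appropriate distribution (i.e., gamma) will be used to study the difference in costs (Beta estimates").
- Effects: "repeated measures will be used to assess the difference (Beta estimates) in health outcomes as a function of the intervention and variables of interest".
- Summary statistic: "The incremental cost-effectiveness ratios (ICER) and incremental cost-utility ratios (ICUR) will be calculated based on beta estimates obtained".
- Uncertainty: "We will carry out a sensitivity analysis for estimated values while considering a range of plausible values (95% CI").
- Reading of the ratio: "The ICUR will quantify the trade-off between costs and health-related quality of life".

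The evaluation "will be carried out from health system and patient perspectives based on Canadian guidelines [77"]. The content of those guidelines is not reproduced. The section says nothing else about the uncertainty of the ratios, and it does not say which of the estimated values are varied or whether they are varied together.

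**The concern.** A superiority question needs a measure of uncertainty for the comparison of costs and effects taken together. The stated method places 95% CI ranges around the ingredients of a ratio, or around the ratio itself. There are two difficulties.

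1. A ratio whose denominator can be zero has no ordered range. As the incremental effect moves from positive to negative, the ratio runs off to infinity on one side and returns from infinity with the opposite sign on the other. A negative value is ambiguous by itself: it arises both when SMS is cheaper and better and when it is dearer and worse.
2. Costs and effects come from the same patients and are usually correlated. Moving each over its own interval treats the corners of a rectangle as plausible, whatever the data say about their joint distribution.

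At stake is the readability of a secondary result that the Discussion presents as evidence for policy makers and managers. The primary outcome is not affected.

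**Working it through.** **Inputs from the document.** The Sample size section gives a difference of 4 BAI points, SD 12.5, d = 4/12.5 = 0.32, 80% power, α = 0.05, 155 per group, 25% attrition and 207 per arm. It also gives power of at least 76% after allowing for an ICC of 0.02. The Participant timeline section gives a retention target of less than 5% attrition. No effect size or SD is given for AQoL-6D utility, anxiety-free days or costs.

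**The plan's own figure.** A two-sided two-sample t-test with d = 0.32 has power 0.799 at 154 per group and 0.802 at 155, so 155 reproduces. 155/0.75 = 206.7, which rounds up to 207.

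**How often the effect interval includes zero.** For a standardised between-arm effect d with n analysed per arm, SE = √(2/n) and

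P(95% CI includes 0) ≈ Φ(1.96 − d/SE), the far tail being negligible.

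For n = 155, SE = √(2/155) = 0.1136. If the attrition target is met, n = 207 × 0.95 ≈ 197 and SE = √(2/197) = 0.1008.

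| d | Source | n = 155 | n = 197 |
|---|---|---|---|
| 0.32 | design effect for the BAI | Φ(1.96 − 2.817) = 0.20 | Φ(1.96 − 3.176) = 0.11 |
| 0.20 | assumed | Φ(1.96 − 1.761) = 0.58 | Φ(1.96 − 1.985) = 0.49 |
| 0.10 | assumed | Φ(1.96 − 0.880) = 0.86 | Φ(1.96 − 0.992) = 0.83 |

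The 0.20 is simply the complement of the 80% design power. With the plan's own allowance for clustering it is at most 1 − 0.76 = 0.24.

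**What then happens to the ratio.** This part is an illustration, and every input is assumed: incremental cost ΔC = 500 dollars (SE 300) and incremental effect ΔE = 0.02 QALY (SE 0.015).

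- 95% CI of ΔE: 0.02 ± 1.96 × 0.015 = −0.0094 to 0.0494.
- Ratio at the point estimate: 500/0.02 = 25,000.
- Ratio at the upper limit: 500/0.0494 = 10,121.
- Ratio at the lower limit: 500/(−0.0094) = −53,191.
- In between: 500/0.001 = 500,000 and 500/(−0.001) = −500,000, without bound as ΔE approaches zero.

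The values at the two limits do not bracket the point estimate, so they do not form an interval. If instead the SE of ΔE is 0.008, its interval is 0.0043 to 0.0357 and, with ΔC fixed, the ratio runs from 14,013 to 115,741. That range is wide but orderly. The failure therefore depends on whether zero lies inside the effect interval.

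**Net benefit on the first set of inputs (SE of ΔE 0.015).** INB = λΔE − ΔC, with variance (λ·SE_E)² + SE_C² − 2ρ·λ·SE_E·SE_C, where ρ is the correlation between the two estimates.

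- λ = 50,000, ρ = 0: INB = 1,000 − 500 = 500; SE = √(750² + 300²) = 808; 95% CI −1,083 to 2,083; probability of a positive net benefit 0.73.
- λ = 20,000, ρ = 0: INB = 400 − 500 = −100; SE = √(300² + 300²) = 424; 95% CI −932 to 732; probability 0.41.
- λ = 50,000, assumed ρ = 0.5: SE = √(652,500 − 225,000) = 654. With ρ = −0.5: SE = √(652,500 + 225,000) = 937.

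Net benefit stays defined and ordered although the effect interval includes zero. The last line shows what is lost when the correlation is ignored: the SE moves from 654 to 937 on the same marginal inputs.

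**The case against.** The strongest reply is that the sentence is ambiguous. It is labelled a sensitivity analysis, does not name the values varied, and does not say that the ratio will be reported as an interval. Varying cost inputs with the effect held at its estimate meets no discontinuity. This stands in part. However, the sentence follows shortly after the one forming the ratios from the beta estimates, and it speaks of estimated values with 95% CIs. It most naturally refers to the betas or the ratios. If only unit costs were meant, the article would state no method for the sampling uncertainty of the ratio.

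A reader might also infer three stronger points, which the document does not support:

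- *That the ICER and ICUR are undefined.* They are ratios of point estimates and are defined unless the estimated effect is exactly zero. Only the range fails. The sign ambiguity disappears once incremental cost and incremental effect are reported separately, and the plan estimates both.
- *That question (b) cannot be answered.* If SMS + TAU costs less and does more, or the reverse, no threshold is needed. Showing dominance with its uncertainty still calls for a joint analysis.
- *That the absence of a willingness-to-pay value is an error.* A condensed article may leave this to a full protocol or economic plan, and this one refers to Canadian guidelines. It is not a finding in itself.

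Finally, the probabilities for effects smaller than d = 0.32 rest on assumption, and the calculation uses an unadjusted comparison where the plan has repeated-measures models. That is correct, and it limits how precisely the size of the problem can be stated.

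**Conclusion.** The concern holds in a limited form: the one uncertainty method stated for the economic evaluation is poorly matched to a superiority question. Under the natural reading of the sentence, the range of the ratio is unbounded or disjoint whenever the effect interval includes zero, and separate intervals leave out the correlation of costs and effects.

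The only size that rests on the document's own figures is about 20% at d = 0.32 with 155 analysed per arm: at most 24% with the plan's clustering allowance, and about 11% if the retention target is met. Even this borrows the BAI design effect for the economic outcomes. For utility or anxiety-free days the true effect could be smaller, and the chance is then 58% at d = 0.20 or 86% at d = 0.10 with 155 per arm. Correcting this is a cheap improvement to a secondary analysis; the trial's main conclusion does not depend on it.

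**What to change.** In the section on economic evaluation outcomes:

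1. Keep the ICER and ICUR as point summaries, always reported with incremental cost and incremental effect.
2. Replace the 95% CI range as the measure of sampling uncertainty with incremental net benefit, λ × incremental effect − incremental cost in dollars. Compute it over a range of λ stated in advance, one range per QALY and one per anxiety-free day.
3. Take the 95% CI of net benefit, and a cost-effectiveness acceptability curve, from a bootstrap that resamples each patient's costs and effects together and keeps SMS groups intact.
4. If a sensitivity analysis on inputs such as unit costs is also wanted, name the values to be varied and keep it separate from sampling uncertainty.

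No new data are needed. The costs are some programming and choosing the λ ranges before the results are known. With 10 to 15 patients per group, 207 patients make about 14 to 21 SMS groups (207/15 = 13.8; 207/10 = 20.7). Resampling whole groups is feasible but somewhat coarse. If a fuller economic plan already specifies this, a one-line reference to it is sufficient.

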### Trial coordination

The trial coordinating center will be at Université de Sherbrooke. The executive committee will be composed of the principal investigators, the principal knowledge user (or representative), and research coordinator, with web meetings every two to three weeks throughout the four years of the project, an efficient management strategy for multi-centric trials. A Steering committee (i.e., co-investigators and co-knowledge users) will meet at strategic decision-making points throughout the trial.

### Dissemination policy

We have adopted an integrated knowledge transfer (KT) strategy in which knowledge users are integral team members and participate in the complete research process. We have established a collaboration with the Relief community organization - involved in the design of the study, full members of the research team, and involved as knowledge users throughout all project phases. Other collaborators, including national, provincial, and regional decision makers, clinicians, and patient-partners for the advisory board, will also contribute specific expertise to integrated knowledge application. All knowledge users will be involved in making decisions concerning data collection, analyses, interpretation of results and knowledge transfer. The detailed KT plan for the study will include activities for the public, organizations/professionals, and scientific community. We will follow best practices recommended by scientific journals to determine authorship in publications.

### Monitoring Steering committee

The study will be overseen by an independent data and safety monitoring committee (DSMC) consisting of three members with collective expertise in statistics, health services research, and anxiety disorders. No interim analyses will be conducted. The Data Safety and Monitoring Committee (DSMC) could request allocation data for a specific participant in case of an incident. The DSMC will monitor patient recruitment, retention and adverse events using a prespecified adverse event reporting protocol. The DSMC will also conduct a semi-annual audit.

## Discussion

To our knowledge, this is the first randomized controlled trial to examine the effectiveness of a structured group SMS program specifically developed for anxiety disorders as a complement to usual care. The SMS intervention developed by Relief for anxiety disorders could promote personal recovery through psychoeducation, strategies for day-to-day symptoms management, self-efficacy and empowerment. In response to the knowledge gap about the added value of structured group SMS for anxiety disorders in community-based care, we have established a strong collaboration between researchers and knowledge users to address this question. This partnership will help us provide relevant data to knowledge users to increase the uptake of trial results. In Québec, this group-based SMS program for anxiety disorders developed and implemented by Relief has demonstrated good uptake, even without evidence-based data regarding the benefits of SMS as a complementary intervention for individuals with anxiety disorders. Moderator and mediator analysis will also provide informative hypothesis generating data for future trials to examine sociodemographic and clinical characteristics associated with SMS effectiveness, but also with regards to previous treatment experience. As there is an overlap between SMS and low-intensity psychotherapy interventions, this may provide interesting health services research hypothesis to inform future studies. Therefore, we will conduct this pragmatic randomized controlled trial to document potential benefits of SMS for individuals experiencing anxiety disorders with extensive patient-reported outcome measures as well as with health system data to inform policy makers, health care managers, clinicians, and patients on the potential impact of the intervention. The Relief community organization is committed to submitting the added value of the group SMS program to a rigorous evaluation, to share results to partner organizations as well as to review the methodology and content of the SMS intervention in case of negative results. A rigorous evaluation of the effectiveness and cost-effectiveness of SMS as a complement to treatment-as-usual could have a significant impact on evidence-based decision-making of stakeholders considering the upward emphasis on a personal recovery-based approach in mental health.

## Data Availability

The datasets generated during the current study will not be publicly available due to ethics committee regulations, but will be available from the corresponding author on reasonable request.

## Abbreviations

AFD: Anxiety-free days
AQol-6D: Assessment of Quality of Life – 6D
BAI: Beck Anxiety Inventory
BDCU: Quebec emergency department database
CBT: Cognitive behavioural therapy
CRCHUS: Centre de recherche du Centre Hospitalier Universitaire de Sherbrooke
DSM-5: Diagnostic and Statistical Manual of Mental Disorders, 5th edition
DSMC: Data and safety monitoring committee
GAD-7: Generalised Anxiety Disorder Questionnaire
GCS: Gross Cohesion Scale
GLM: Generalized linear models
ICER: Incremental cost-effectiveness ratios
ICUR: Incremental cost-utility ratios
KT: Knowledge transfer
MHSQ: Mental Health Self-Management Questionnaire
MINI: Mini International Neuropsychiatric Interview
PDSS-SR: Panic Disorder Severity Scale Self Report
PHQ-9: Patient Health Questionnaire
RAMQ: Régie de l’assurance-maladie du Québec
RAS-r: Recovery Assessment Scale – revised
RCT: Randomized controlled trial
SMS: Self-management support
SPIN: Social Phobia Inventory
TAU: Treatment-as-usual
WAI: Working Alliance Inventory
